## Abstract

To achieve global hepatitis elimination by 2030, it is critical to prevent the mother-to-child transmission (MTCT) of hepatitis B virus (HBV). Since 2009, the WHO has recommended administering hepatitis B vaccine to all neonates within 24 h of birth to prevent MTCT. However, many countries in sub-Saharan Africa only provide hepatitis B immunization at the age of 6, 10, and 14 weeks or 8, 12, and 16 weeks using a combined vaccine. To accelerate the introduction of the hepatitis B birth dose vaccine (HepB-BD) into sub-Saharan Africa, it is critical to establish to what extent the addition of HepB-BD can further reduce HBV transmission in areas where three-dose infant vaccination has been implemented. We therefore designed a study to evaluate the impact, acceptability, and cost-effectiveness of incorporating the HepB-BD into the routine immunization program in a real-life field condition in Burkina Faso, where the hepatitis B vaccination is currently scheduled at 8-12-16 weeks. Through a multidisciplinary approach combining epidemiology, anthropology, and health economics, the Neonatal Vaccination against Hepatitis B in Africa (NéoVac) study conducts a pragmatic stepped wedge cluster randomized controlled trial in rural areas of the Hauts-Bassins Region. The study was registered in ClinicalTrials.gov (identifier: NCT04029454). A health center is designated as a cluster, and the introduction of HepB-BD will be rolled out sequentially in 24 centers. Following an initial period in which no health center administers HepB-BD, one center will be randomly allocated to incorporate HepB-BD. Then, at a regular interval, another center will be randomized to cross from the control to the intervention period, until all 24 centers integrate HepB-BD. Pregnant women attending antenatal care will be systematically invited to participate. Infants born during the control period will follow the conventional immunization schedule (8-12-16 weeks), while those born in the interventional period will receive HepB-BD in addition to the routine vaccines (0-8-12-16 weeks). The primary outcome, the proportion of hepatitis B surface antigen (HBsAg) positivity in infants aged at 9 months, will be compared between children born before and after HepB-BD introduction. The study will generate data that may assist governments and stakeholders in sub-Saharan Africa to make evidence-based decisions about whether to add HepB-BD into the national immunization programs.

## 1. Introduction

Viral hepatitis is a serious global health concern. In 2015, the World Health Organization (WHO) estimated that 1.34 million people died from viral hepatitis [1]. This is the seventh leading cause of death in the world and is ranked higher than HIV, tuberculosis, and malaria [2]. Most of these deaths occur in low-income and middle-income countries (LMIC), and more than half are attributable to chronic infection with hepatitis B virus (HBV) [1]. In 2016, the WHO adopted a strategy to globally eliminate HBV infection as a public health threat by 2030, with a goal of reducing its incidence by 90% and its mortality by 65% [3]. To reach these targets, it is crucial to eliminate the mother-to-child transmission (MTCT) of HBV, because chronic HBV infection develops more frequently when infection occurs early during childhood, especially at birth through MTCT [4,5]. Moreover, the natural history of chronic HBV infection is likely to differ depending on the mode of transmission; those who acquired chronic HBV infection through MTCT may have a higher risk of prolonged viral replication, cirrhosis and hepatocellular carcinoma (HCC) than those who acquired chronic infection through horizontal transmission [6,7,8,9].

To prevent MTCT, the WHO recommends that all neonates, regardless of maternal HBV infection, receive their first dose of the hepatitis B vaccine as soon as possible after birth, preferably within 24 h, as a monovalent formulation [10]. This hepatitis B birth dose vaccine (HepB-BD) should be followed by at least two additional doses that can be given as a monovalent or as part of a combined vaccine [10]. Most countries worldwide already integrated in their immunization programs three doses of the infant hepatitis B vaccine as a combined vaccine (pentavalent: DTP-HepB-Hib, or hexavalent formulation: DTPa-HepB-IPV-Hib) scheduled at the age of 6-10-14 weeks or 8-12-16 weeks [11]. However, access to the birth dose monovalent vaccine is still limited in many LMICs, particularly in sub-Saharan Africa, for several reasons. First, among the 47 countries in the WHO African Region, only 13 have introduced by 2020 the monovalent hepatitis B vaccination scheduled at birth [12]. This situation is partly explained by the lack of financial support; Gavi, the Vaccine Alliance, has been supporting the pentavalent vaccines but not yet the monovalent hepatitis B vaccines, because the price of the monovalent vaccine per dose is below the minimum country co-financing level ($0.20) and is thus not eligible for the Gavi [13]. Nevertheless, the Gavi will hopefully soon support strengthening the country’s vaccine delivery system to implement its timely administration within 24 h of birth [14]. Second, even a few African countries that have integrated HepB-BD in their programs have been facing difficulties in its timely administration within 24 h after birth [15] due to the high rate of child delivery at home [16,17].

More importantly, the evidence base to support the WHO’s recommendation to start immunizing immediately after birth, rather than later at 6–8 weeks of life, is limited. First, most randomized controlled trials (RCTs) evaluating the efficacy of the vaccine series starting at birth have used a control group with a placebo or without any hepatitis B vaccine administration. A meta-analysis of RCTs indicated that among infants born to HBV-infected mothers, those who received the first dose at birth are 3.5 times less likely to be infected than those who did not receive any dose of the hepatitis B vaccine (relative risk: 0.28, 95% CI: 0.20–0.40) [18]. However, this finding is not informative for a country where the hepatitis B vaccination series is currently scheduled at 6-10-14 weeks or 8-12-16 weeks, and the future introduction of HepB-BD is carefully examined; the question in such a country is to what extent the program can further prevent HBV infections by adding the monovalent HepB-BD to three doses of the combined vaccines. Second, the WHO recently conducted a systematic review of RCTs and prospective observational studies to evaluate the efficacy of the vaccine administered within 24 h of life compared to the vaccine administered after 24 h [19]. This review identified only one nonrandomized interventional study conducted by Ekra et al. in Côte d’Ivoire, which compared two vaccination schedules: 0-6-14 weeks (interventional arm with HepB-BD) and 6-10-14 weeks (control arm without HepB-BD). The study did not observe a statistically significant difference in HBsAg positivity in infants aged 9 months between the groups: 0.5% (9/1896) with HepB-BD and 0.5% (10/1900) without HepB-BD [20]. Finally, the WHO’s HepB-BD recommendation has been based on a single retrospective study in Canada [10,21]. Marion et al. studied children born to HBsAg-positive mothers, and found an increased risk of MTCT with age at the first dose (1–3, 4–7, 8–61, and ≥62 days with an odds ratio of 3.3 (95% CI: 1.3–8.2) for each unit increase in age group) [22]. The retrospective design of this study, however, poses a risk of selection bias and does not provide a satisfactory level of evidence.

Consequently, we aim to conduct a stepped wedge cluster randomized controlled trial to assess the impact of incorporating the monovalent HepB-BD into the infant immunization program on the risk of HBV MTCT under real-life field conditions in Burkina Faso, where the hepatitis B vaccination is currently scheduled at 8-12-16 weeks of life. We also assessed the acceptability of the intervention and its cost-effectiveness by adopting a multidisciplinary approach combining epidemiology, anthropology, and health economics.

## 2. Methods

### 2.1. NéoVac Research Program

Neonatal Vaccination against Hepatitis B in Africa study (NéoVac), funded by the Total Foundation, is a research program originally started in 2015 in Senegal, Burkina Faso, and Madagascar, where the hepatitis B vaccination series have been scheduled at 6-10-14 weeks (Senegal and Madagascar) or 8-12-16 weeks (Burkina Faso), without HepB-BD. The aim of the program was to develop and evaluate a strategy to implement the timely administration of HepB-BD in these countries. The program was designed in two successive steps. Step 1, the formative phase, collects epidemiological, anthropological, and economic data in each country in order to develop a locally adapted, sustainable strategy for providing timely HepB-BD within 24 h of birth. This step is followed by Step 2 to evaluate the impact of the strategy to reduce the risk of HBV infection in infants. In Burkina Faso, Step 1 was conducted in Dafra District, Hauts-Bassins Region, in 2016–2017. The epidemiological study found approximately 90% of children born at health facilities, and 86% completed three doses of the pentavalent vaccine. The anthropological study observed that infant vaccination was widely accepted in the communities, and the economic study suggested that the costs of introducing HepB-BD would be relatively low compared to the introduction costs of other vaccines [23]. These results were presented at the steering committee organized by the study investigators in Ouagadougou on 20 Nov 2017, with local healthcare workers, researchers, civil society organizations, the Ministry of Health, and the WHO. Due to a high rate of institutional delivery in the study zone, the committee considered that the administration of HepB-BD in maternity services at health centers would result in good coverage of timely HepB-BD. However, the committee questioned to what extent the addition of HepB-BD would further prevent infant HBV infection. Consequently, the overall objectives of Step 2 were defined as follows: to assess the impact of adding HepB-BD to the current hepatitis B vaccination schedule at 8-12-16 weeks of life on the risk of MTCT, and to evaluate its acceptability among healthcare workers and community members, and its cost-effectiveness.

### 2.2. Specific Objectives

The study included three work packages (epidemiology, anthropology, the health economics) funded by the Total Foundation. Each has specific objectives described below. The NéoVac program has an ancillary study called “Performance of Diagnostic Test for Hepatitis B in Africa (PREDICT-B)” funded by Gilead Sciences and Abbott. This sub-study is described at the end of Section 2.

Work package (1) Epidemiology:
-To assess the effectiveness of introducing HepB-BD on the risk of MTCT, defined as positive HBsAg in infants aged 9 months;-To assess the impact of introducing HepB-BD on the risk of MTCT in subgroups of mother–child pairs defined by the maternal HBsAg;-To assess the impact of introducing HepB-BD on the risk of MTCT in subgroups of mother–child pairs defined by the maternal hepatitis B e antigen (HBeAg) and HBV DNA levels;-To explore the dose–response relationship between the number of hepatitis B vaccine doses administered (0–4) and the risk of HBsAg positivity in infants;-To examine the association between the timeliness of the first dose of the hepatitis B vaccine and the risk of HBsAg positivity in infants;-To compare the immunological response between those who received HepB-BD and those who did not by titration of the antibody to HBsAg (anti-HBs) in infants;-To describe the coverage and timeliness of HepB-BD, pentavalent vaccines, and other vaccines recommended by the national infant immunization program in Burkina Faso;-To estimate the prevalence of HBsAg in mothers of children aged 9 months;-To estimate the prevalence of HBeAg in HBsAg-positive mothers;-To estimate the prevalence of HBV DNA levels ≥200,000 IU/mL in HBsAg-positive mothers.

Work package (2) Anthropology:
-To evaluate the acceptability of adding HepB-BD into the infant immunization program among healthcare workers and community members.

Work package (3) Health economics:
-To evaluate the public health benefits, the cost, and the cost-effectiveness of introducing HepB-BD into the infant immunization program in Burkina Faso versus the current situation.

### 2.3. Study Design

#### 2.3.1. Stepped Wedge Cluster Randomized Trial

The current protocol was developed in accordance with the CONSORT 2010 extension to cluster randomized trials [24] and the modifications specific to the stepped wedge design proposed by Hemming et al. [25]. The protocol was registered with ClinicalTrials.gov (identifier: NCT04029454), and it was reported according to the SPIRIT 2013 Statement [26]. In this multicenter stepped wedge cluster randomized controlled trial, the cluster unit is a health center (Centre de Santé et de Promotion Sociale: CSPS), a primary healthcare facility that pregnant women routinely visit for antenatal care, child delivery, and child immunization in Burkina Faso. The introduction of HepB-BD will be rolled out sequentially in 24 CSPSs in the Hauts-Bassins Region. Following an initial period in which no CSPS administers HepB-BD, one CSPS will be randomly allocated to incorporate HepB-BD into the infant immunization schedule. Then, at a regular interval of 3 weeks, another CSPS will be randomized to cross from the control period to the intervention period. This process will be repeated until all 24 CSPSs have crossed over to the intervention period (Figure 1). Other vaccines recommended by the national immunization program, including three doses of the pentavalent vaccine, will be systematically provided throughout the study period as part of the routine practice. The stepped wedge design was retained by the steering committee based on the following rationales.

#### 2.3.2. Why Cluster Randomized Trial Rather Than Individually Randomized Trial?

This is a pragmatic trial to evaluate a whole service delivery intervention that is “complex”. The intervention includes not only the administration of monovalent vaccines to newborns in a timely manner, but also the vaccine supply, storage, training of healthcare workers, and communication with pregnant women/mothers. The cluster design was chosen as it is logistically more convenient to provide the intervention at the CSPS level, rather than at the individual level. This design also enables us to limit the risk of contamination (i.e., individuals in the control group receive the intervention, and vice versa) that is more likely to happen when healthcare workers in the same facility simultaneously provide two different strategies [27].

#### 2.3.3. Why Stepped Wedge Rather Than Parallel Design?

As discussed in the introduction, the evidence supporting the addition of HepB-BD to the conventional vaccination series is limited. Nevertheless, there has been an established WHO recommendation to administer HepB-BD to all newborns. The stepped wedge design has the advantage of making all CSPSs benefit from the intervention by the end of the trial, which is politically and ethically more acceptable than the parallel cluster randomized trials, in which half of clusters do not receive the intervention for the duration of the study [25]. Moreover, the sequential rollout has fewer logistical constraints, avoiding an overcommitment of human and financial resources in comparison to the instantaneous implementation.

### 2.4. Study Setting

The trial will be conducted in two districts in the Hauts-Bassins Region, called Dô and Dafra, where an estimated 548,000 and 348,000 people lived in 2017, respectively (Figure 2). In Dô, there is one district hospital (Centre Médical avec Antenne Chirurgicale: CMA) and 28 CSPSs. In Dafra, there is one district hospital and 16 CSPSs. Each CSPS has a well-demarcated area of operation, but with population sizes that differ substantially. Consequently, each CSPS has a varying number of staff, but normally includes a chief nurse, nurses, midwives, auxiliary midwives, and mobile health workers (agent itinérant de santé: AIS). The CSPS is the primary contact between communities and the healthcare system, whilst complicated cases are referred to the district hospital where there are medical doctors. At CSPS, the antenatal care, child delivery, and child immunization are commonly shared between staff members who have a different qualification.

### 2.5. Eligibility Criteria

#### 2.5.1. Clusters

CSPSs are eligible if they are located in the rural/semi-rural zone of the Dô and Dafra districts, and they are accessible from our research center (Centre Muraz, located in Bobo-Dioulasso) all-year-round, including the rainy season. We finally selected a total of 24 CSPSs: 16 from Dô and 8 from Dafra, that met the criteria above.

#### 2.5.2. Individuals

All pregnant women of any age living in the area covered by the study CSPSs, who attended the antenatal care or gave birth at one of the study CSPSs, and who gave a written informed consent will be included. Exclusion criteria include a miscarriage, abortion, stillbirth, neonatal defect incompatible with life and any maternal or child health condition incompatible with the research activities. They will be also excluded if they had participated in other clinical trials that are incompatible with this trial.

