#### 2.6.2. Control Period

During the control period, there will be no supply of the monovalent vaccines to the CSPS; therefore, babies born during this period in the catchment area of this CSPS will not receive HepB-BD.

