### 2.8. Participant Flow

#### 2.8.1. First Visit (V1)

The participant flow is schematically presented in Figure 3. Whenever a pregnant woman visits a study CSPS for antenatal care, she will be assessed for her eligibility and will be invited to participate in the study. Women coming directly to a CSPS for delivery without a prior antenatal care visit will be invited to participate immediately after the child delivery. Using a participant information sheet written in French (Document S1) and an illustrated information sheet (Document S2), healthcare workers will explain the study to all potentially eligible pregnant women in a local language. Women aged ≥18 years will be asked to sign an informed consent (Document S3). Those aged <18 years will be asked to sign an assent, in addition to an informed consent form that will be signed by her legally authorized representative. Illiterate participants will be asked to provide a fingerprint. Once the informed consent is obtained, sociodemographic data will be collected through an interview with the women, and the case report form (CRF) for V1 will be filled (Document S4).

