### 2.10. Assignment of Intervention

The chronological order in which a CSPS crosses over to the intervention will be randomized by a statistician at the Institut Pasteur, Paris, using the STATA^®^ version 15.0 (StataCorp, College Station, TX, USA). To minimize the imbalance between the intervention period and the control period, stratification will be performed by the districts (Dafra, *n* = 8; and Dô, *n* = 16). The list of the CSPS with its order will be kept in Paris, and will only be accessible by the study statistician. The intervention start date of each CSPS will be concealed from all the investigators, healthcare workers, and study participants, except the statistician. Two weeks prior to the date of the crossover from the control to the intervention, the statistician will inform the investigators about the next CSPS that will start the intervention. The study coordinator will then notify this CSPS of the intervention start date. This will ensure sufficient time for the delivery of the vaccines to the next CSPS and for the healthcare workers in this CSPS to be ready to start administering HepB-BD.

While a CSPS is in the control period, nobody will know when the intervention will begin in this CSPS. However, once CSPS has crossed over to the intervention, both the investigators and the healthcare workers in this CSPS will know that HepB-BD is now available and given in this CSPS. To limit the risk of selection bias during the enrolment of study participants, healthcare workers will inform pregnant women about the possibility of their child being vaccinated at birth, in the same way during the control and intervention period. However, despite such a precaution, if the pregnant woman spontaneously asks about the allocation status of the CSPS, the healthcare workers will tell her whether the intervention has already been assigned to this CSPS or not.

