### 2.12. Statistical Methods

Using an intention-to-treat analysis involving all mother–child pairs included in the study, the impact of introducing monovalent hepatitis B vaccines at birth on the risk of MTCT will be estimated by comparing the proportion of children positive for HBsAg at the age of 9 months between two groups: children born before the introduction of HepB-BD into their CSPS (control arm) and those born after their CSPS begins HepB-BD (intervention arm), regardless of whether or not they have received HepB-BD according to the assignment of the intervention to their CSPS. Our primary analysis will be “complete case analysis” excluding those with missing outcomes as it is unlikely that maternal HBV infection, the leading factor for the vaccine failure, is related with a loss to follow-up [40,41]. We will also conduct a sensitivity analysis with an extreme assumption that all those lost to follow-up were infected with HBV.

A per-protocol analysis will also be performed by restricting the analysis to children born before the introduction of HepB-BD into their CSPS and not having received HepB-BD, or to those born after the introduction of HepB-BD into their CSPS and who have received HepB-BD. To account for the calendar time and for the correlations between individuals within the same cluster, a logistic regression model with a random effect for clusters and a fixed effect for each step will be fitted [25]. All the analyses will be performed using STATA^®^.

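### Consent after delivery and an open-ended health exclusion let entry to the intention-to-treat set depend on the arm; the likely bias is small and cheap to close off

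*Protocol article*

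**What the plan says.** **Who enters.** Section 2.5.2 takes pregnant women living in the catchment "who attended the antenatal care or gave birth at one of the study CSPSs, and who gave a written informed consent will be included". Its exclusions are miscarriage, abortion, stillbirth, "neonatal defect incompatible with life and any maternal or child health condition incompatible with the research activities", and participation in an incompatible trial.

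**When consent is sought.** Most women are invited at antenatal care. Section 2.8.1 adds a second route: "Women coming directly to a CSPS for delivery without a prior antenatal care visit will be invited to participate immediately after the child delivery".

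**What fixes the arm.** Sections 2.8.2 and 2.12 assign the infant by date of birth relative to the crossover of its health centre (CSPS).

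**Who knows the arm.** In a control period, Section 2.6.2 says "there will be no supply of the monovalent vaccines to the CSPS", so staff can see that the intervention has not begun. About two weeks before crossover, Section 2.10 says, "The study coordinator will then notify this CSPS of the intervention start date". Afterwards, "both the investigators and the healthcare workers in this CSPS will know that HepB-BD is now available and given in this CSPS".

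**Who is analysed.** Section 2.12 plans the comparison "Using an intention-to-treat analysis involving all mother–child pairs included in the study". The primary analysis is complete-case, with a sensitivity analysis that counts everyone lost to follow-up as infected.

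**Safeguard.** Section 2.10 recognises selection bias at enrolment. Crossover dates are concealed until notice is given, and pregnant women hear the same information in both periods. A woman who asks is told the centre's status.

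**The concern.** An intention-to-treat comparison protects against selection only from the moment a participant is in the set. Here some entry decisions come after the arm is settled and are made by staff who know it.

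There are two openings. First, a delivery-route woman is approached and consents once her infant has already been born into a known arm. Second, the exclusion for a maternal or child health condition has no stated threshold. Its child part can in practice be judged only around or after birth. The research activities at the birth visit also differ between the arms, since one includes a vaccination and the other does not, so incompatibility need not be read the same way in both.

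Pairs that are never consented, or are excluded after birth, leave both numerator and denominator. The same-information rule does not govern whom staff approach after delivery or how they apply the exclusion. The sensitivity analysis for loss to follow-up reaches only pairs that were included. With planned risks near 1% and below, a modest difference in who enters could shift the estimate.

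**Working it through.** **1. The plan's own figures (Section 2.9).**
- Control risk: 0.10 × 0.15 × 0.60 + 0.10 × 0.85 × 0.05 = 0.01325, stated as 1.33%.
- Intervention risk: 0.10 × 0.15 × 0.20 + 0 = 0.00300, stated as 0.30%.
- Infants per cluster-period: 22 × 0.90 × 3/4 = 14.85, stated as 14.8.
- Power: the Hussey-Hughes stepped wedge formula (24 clusters, 25 periods, CV 0.40, variance at the control risk, two-sided 5%) gives 85.0% at 14.8 infants and 80.9% at 13. The plan states 84% and 80%, so its figures reproduce closely.
- Planned risk ratio: 0.00300 / 0.01325 = 0.226.

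**2. Expected infections.** One cluster crosses per step, so 24 × 25 = 600 cluster-periods split into 300 control and 300 intervention.
- Infants per arm: 300 × 14.8 = 4,440.
- Control infections: 4,440 × 0.01325 = 58.8.
- Intervention infections: 4,440 × 0.00300 = 13.3.

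The plan's total of about 8,500 is nearer 24 × 24 × 14.8 = 8,525 than 8,880. This does not affect the percentages below.

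**3. Discretionary exclusion in one arm.** Remove a fraction f of intervention infants whose risk is r times average. The remaining risk is multiplied by (1 − r·f)/(1 − f). The documents give neither f nor r; both are assumed.

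| f | r | Multiplier | Fall in intervention risk | Risk ratio |
|---|---|---|---|---|
| 2% | 3 | 0.94/0.98 = 0.959 | 4.1% | 0.217 |
| 5% | 3 | 0.85/0.95 = 0.895 | 10.5% | 0.203 |

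Under no vaccine effect, with f from 1% to 5% and r from 2 to 5, the apparent risk ratio runs from 0.99 (0.98/0.99) to 0.79 (0.75/0.95).

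**4. Differential enrolment by the delivery route.** Let a share s of pairs come by this route, at r times the risk of antenatal-route pairs, with enrolment e0 in control and e1 in intervention. Under no vaccine effect the apparent risk ratio is

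[((1 − s) + s·e1·r) / ((1 − s) + s·e1)] ÷ [((1 − s) + s·e0·r) / ((1 − s) + s·e0)].

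The assumed ranges are s from 2% to 20% and r from 1.5 to 3.
- Enrolment of 90% in one arm and 70% in the other: ratio 0.95 to 1.05. The low end, at s = 20% and r = 3, is (1.22/0.94)/(1.34/0.98) = 0.949.
- Enrolment of 50% in control and 95% in intervention: ratio 1.00 to 1.13. The high end is (1.37/0.99)/(1.10/0.90) = 1.132.

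**5. Scale against sampling error.** Ignoring clustering, SE(log RR) ≈ √(1/58.8 + 1/13.3) = 0.30. The shifts in step 3 are |ln 0.959| = 0.042 and |ln 0.895| = 0.111, or about 0.14 and 0.37 of a standard error.

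**The case against.** The strongest reply is that selection on the main driver of the outcome is hard to imagine. Section 2.6.4 says no centre or district hospital in the zone screens antenatally for HBV, and Section 2.8.3 tests mothers only at the 9-month visit. Staff will generally not know which infants are at risk, so selection would have to act through weak correlates. The threefold risk used above has no support in the documents. This stands, and it is why the likely bias is small.

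The plan is also not without safeguards. Most women are expected to be approached antenatally, and the concealed dates and uniform information give them partial protection. That stands too, but neither measure reaches consent after delivery or the health exclusion.

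Some stronger readings are tempting and are not supported:

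- **A weak newborn who cannot be vaccinated promptly would be dropped in intervention periods.** The exclusion refers to research activities, not vaccination, and Section 2.12 keeps infants in their arm whether or not they received the birth dose.
- **All the exclusions are exposed.** Miscarriage and abortion precede the birth that defines the arm. Stillbirth and a lethal defect leave little room for judgement. The maternal half of the health criterion can be judged at the first visit. The exposed part is the open-ended condition applied to a live-born infant.
- **The bias equals the share of infections lost, 6% or 15%.** The same infants also leave the denominator, which gives 4.1% and 10.5%.

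The article condenses a full protocol that may define the criterion more tightly. As stated, though, the rule is open-ended and carries no threshold.

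**Conclusion.** The point holds as a moderate weakness in two stated rules: consent after birth for delivery-route women, and an open-ended exclusion that can be applied to live-born infants by staff who know the arm. Entry to the intention-to-treat set can therefore depend on the arm. The documents do not show that it will.

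The size is illustrative, since the delivery-route share, the exclusion rate and the relative risks are all assumed. On those assumptions the intervention risk moves by about 4% to 10.5%, well under one standard error.

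A reader might infer that selection at entry could manufacture the planned effect or invalidate the trial. It could not plausibly do so: the planned ratio is 0.23, while the widest null-effect distortion computed here is 0.79. It would matter more if the true effect were much smaller than planned. The comparison cited in the Introduction, with 0.5% in both groups, shows that this cannot be dismissed.

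**What to change.** **(a) Section 2.5.2.** Allow no discretionary exclusion of a live-born infant after birth. Keep every live-born infant of a consented woman in the intention-to-treat set, in the arm given by its birth date. Where death, a lethal defect or illness prevents the 9-month test, record a missing outcome with its reason. In the extreme-case analysis of Section 2.12, report deaths and lethal defects separately from loss to follow-up, so that they are not simply counted as HBV infections. This concerns the analysis set only and leaves clinical decisions untouched.

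**(b) Section 2.12.** Add a sensitivity analysis of the primary outcome limited, in both arms alike, to women whose first-visit consent was given antenatally, before the birth. The dates needed are already collected. Cutting instead at consent before the crossover notice would be unsound: it would keep nearly all delivery-route women and late bookers of the control periods while dropping their intervention counterparts. The antenatal restriction removes the delivery route evenly. It does not remove staff knowledge of the centre's status when inviting women antenatally, for which the safeguards in Section 2.10 remain the protection.

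**Cost.** One eligibility sentence and one extra analysis on existing data. Missing outcomes rise slightly, and the sensitivity analysis is somewhat less precise than the primary one.
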